### Strategies to improve adherence to interventions {11c}

Overall, a high level of compliance is expected in this study due to the patients’ long previous history of pain burden. In addition, compliance will be promoted by the fact that LIPUS treatment is pain-free, and the device is small and easy to handle and transport (e.g., also on vacation). In addition, compliance with the daily use of ultrasound treatment will be displayed to patients and investigators via the ultrasound device so that prompt countermeasures will be taken if compliance should be insufficient. This involves reminding the study sites to contact the patients via the central data management system. Lastly, compliance will be promoted by the fact that travel expenses of up to EUR 200 per patient can be reimbursed.

### Relevant concomitant care permitted or prohibited during the trial {11d}

Patients will be informed about which medications or additional interventions they may or may not take in this study. This applies to cytostatic drugs which are an inadmissible concomitant medication in this study as well as therapies other than the intervention mentioned and the surgical treatment described, which are also intended to stimulate bone healing (such as shock waves), and are not permitted during the study. Systemic diseases (e.g., diabetes mellitus) and other medications that may have an influence on bone healing (e.g. non-steroidal anti-inflammatory drugs) will be documented. Accompanying physiotherapy and rehabilitation measures before and during the study to improve the function of the affected extremity will be permitted and desired. Surgical revision for persistent non-union without any improvement in routine imaging should be performed at the earliest four months after the index operation or after the start of treatment with LIPUS. This also corresponds to standard treatment without study participation.

### Provisions for post-trial care {30}

After completion of the study, patients will be allowed to continue LIPUS therapy if consolidation is incomplete but progressing. Patients will be insured as part of the study in case of harm. The insurance will also include a commuting accident insurance.

### Outcomes {12}

#### Primary outcome

The primary outcome will be fracture healing 12 months after the start of treatment, defined that both, bony consolidation and functional restoration, must be present (composite endpoint):

Bony consolidation is defined as at least three out of four cortices are consolidated based on the radiological findings.

Functional recovery will measured using patient reported outcome measures (PROM) separately for the upper and lower extremity: Disability of Arm, Shoulder and Hand (DASH) score with a minimal clinically important difference (MCID) of 10 points and Lower Extremity Functional Scale (LEFS) with an MCID of 9 points. The primary outcome is met, if either the score will be at least as good as the normative value of the healthy population, depending on age and sex, or if at least an improvement equal to the MCID will be achieved for the respective outcome.

##### Disability of Arm, Shoulder and Hand (DASH) questionnaire:

The DASH questionnaire, which has been established for over 25 years, will be used to record functional limitations of the entire upper limbs. Its validity has been demonstrated by several studies [22, 23]. It consists of 30 questions, which are answered using a 5-point Likert scales of different characteristics. The maximum score is 100, with low scores indicating a minor limitation. The first part comprises questions on the functional capacity of the upper extremities, while the second part requires answers to questions on symptoms. The questionnaire was developed by the American Academy of Orthopedic Surgeons (AAOS) in collaboration with the Council of Musculoskeletal Specialty Societies (COMSS) and the Institute for Work and Health (Toronto, Canada). For this study, the validated German version is used [24]. To assess whether functional restoration is present, the DASH must show an improvement of at least 10 points compared to baseline or the score must be at least as good as the normative value of the healthy population. A study on normative values in the German population serves as the basis for the normative values [24]. Here, the median values of the non-clinical manual sample are considered normative values, depending on age and sex [24]. The norm values for a manually active sample are taken into account, since these are somewhat higher than those for a non-manually active sample are. It is considered a success for all patients if they have at least as good a value as the norm value of the healthy, manually active sample, regardless of whether they are engaged in manual activity or not.

##### Lower Extremity Functional Scale (LEFS) questionnaire:

The LEFS is a validated self-assessment questionnaire that records activity restrictions following lower limb injuries and objectively depicts the course of therapy. It consists of 20 questions on various activities, answered using a 5-point Likert scale (“no difficulties”: 4 points to “extreme difficulties”: 0 points). The maximum achievable score is 80, with a higher score indicating better function. In a Dutch study from 2017, a median score of 77 was determined for 1,014 participants, with only slight differences between women and men (median score 76 and 78) [25]. In this study, the validated German version of the questionnaire will be used, for which a high reliability (ICC: 0.98) and consistency (CA: 0.95) was shown [25]. To assess whether functional production is present, the LEFS must either show an improvement of at least 9 points compared to baseline or the score must be at least as good as the normative value of the healthy population. A study by Dingemans et al. on normative values in the Dutch population serves as the basis for the normative values, as there is no study on normative values in the German population. It is assumed that the Dutch normative values are transferable to the German population. The median values of the healthy sample as a function of age and sex are regarded as normative values [24].

#### Secondary outcomes

##### Time to fracture healing (radiological)

Fracture healing will be recorded in the electronic case report form (eCRF) at each visit and time from baseline to healing (in days) will be calculated for this outcome. Fracture healing will be interval-censored data, as it will not be known when fracture healing will have taken place between visits.

##### Time until full weight bearing is achieved

Full weight bearing will be assumed if the patients can bear their own body weight on the affected lower limb without any aids. Full weight bearing of the upper limb will be confirmed if the patient can perform everyday tasks such as carrying a box of water or lifting 10 kg with the affected arm. The assessment will depend on the performance of the unaffected side, as patients' abilities vary greatly and it is up to the investigator to decide whether full weight-bearing capacity of the upper limb has been reached. Weight bearing will be recorded in the eCRF at each visit and the time span (in days) since baseline will be calculated. If the exact date is not known, the time until the first visit with full weight-bearing load will be considered (interval-censored data).

##### Range of motion

The range of motion of the joints adjacent to the non-union will be documented in all planes of motion using the neutral zero method. The survey forms for upper and lower extremities according to the neutral zero method of the German Social Accident Insurance will be used.

##### Prevalence and intensity of pain in the area of non-union

The prevalence and intensity of pain will be assessed using the Numerical Rating Scale (NRS). On a scale from 0 (no pain) to 10 (worst pain imaginable), patients should indicate their current perception of pain at each study visit. The NRS is a recognized tool for assessing pain intensity in medical practice and research and is recommended by the “Initiative on Methods, Measurement and Pain Assessment in Clinical Trials” (IMMPACT). Furthermore, the use of pain medication will be recorded at each visit.

##### Health-related quality of life

Health-related quality of life Quality of life will be assessed using the German validated version of the Short Form 12 (SF-12). The SF-12 is a generic questionnaire and an abbreviated version of the Short Form 36. It consists of 12 questions divided into eight different dimensions that provide information about the patient's health status [26]. It provides information on general health perception (one question), physical health (two questions), impaired physical role functioning (two questions), physical pain (one question), vitality (one question), mental health (two questions), impaired emotional role functioning (two questions) and social functioning (one question). The questionnaire is widely used in clinical research, as it is easy to complete due to its short completion time of approximately 2.5 min.

##### Occurrence of complications/incidents

At each visit, patients will be asked about complications (e.g., secondary dislocations, material fractures, re-fractures, re-hospitalization) or other incidents.

##### Performance and time until possible (re-)operations or (re-)osteosynthesis/incidence and duration of hospitalization

At each visit, patients will be asked whether and when they have had further operations or other hospital stays in the meantime. Since it can be assumed that the re-operation of the non-union is performed at the respective study center, the corresponding data can be found in the hospital information system of the respective center. Surgeries or hospital stays that were performed externally will be queried and the corresponding letters will be requested from the patients. This data will be used to calculate the time in days until the first (re-)operation and the total duration of the hospital stay in days.

##### Duration and reason for incapacity for work

The duration of incapacity for work will be recorded based on the certificate of incapacity for work. As both the duration and the reason for incapacity for work are important for this study in order to differentiate between incapacity for work due to the non-union and other reasons for incapacity for work, the corresponding data from the certificate of incapacity for work (International Statistical Classification of Diseases and Related Health Problems; ICD.10 code) will be collected. If the attending physician at the respective study site did not issue the certificate of incapacity for work, the patient will be asked to present it to the study team. Alternatively, with the patient's consent, the ICD.10 code will be requested from the physician who issued the certificate.

**Fig. 1 Fig1:**
[figure not shown]
Flow diagram

### Participant timeline {13} (Fig. 1)

Seven visits will take place at the respective study center. During the screening visit, the inclusion and exclusion criteria are checked, and the patient is informed about the study. If these criteria are met, consent is obtained and the patient is randomized into one of the two groups. Patients receiving LIPUS treatment are prescribed an ultrasound device. For patients in the surgical group, preparations for the operation are made (e.g. anesthesia information). After the patient has been randomized, 7–21 days may elapse before the ordered ultrasound device arrives at the study site, or before all preparations for surgery have been completed and a date has been set. If more than four weeks elapse between randomization and the start of ultrasound therapy or surgery, the inclusion and exclusion criteria must be checked again at the baseline visit for possible changes. Repeated imaging is at the discretion of the attending physician and is performed independently of the study.

At the baseline visit (day 0), patients in the intervention group will receive the ultrasound device and will be instructed on the use. In addition, the site of the non-union to be treated by ultrasound will be marked. Before the start of LIPUS treatment or surgery, baseline data will be collected (Fig. 2) and a physical examination will be performed. In both treatment groups, NRS will be used to evaluate the patients’ pain, and questionnaires will be used to assess the general quality of life (SF-12) and the function of the affected limb (DASH or LEFS).

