### Sample size {14}

Sample size estimation is based on a Z-test with non-pooled variances to verify the non-inferiority of treatment with LIPUS compared to surgical treatment. A fracture-healing rate of 86% is assumed in the surgical treatment group based on previous studies [6]. In the intervention group, a fracture healing rate of 75% is assumed [6, 9–14]. Since spontaneous healing, i.e. healing without treatment, only occurs in an estimated 5% of cases, it can be assumed that both treatments are superior to no treatment.

LIPUS treatment is assumed non-inferior to surgical treatment if the proportion of fracture healings in the intervention treatment group is less than 25 percentage points lower than in the control group. If a fracture-healing rate of 86% is assumed with surgical treatment and LIPUS treatment is actually non-inferior to surgical treatment, this means that fracture healing can be expected in more than 61% of those treated with LIPUS. In these, surgical intervention can be avoided and all the risks associated with it (e.g., re-hospitalization, secondary diseases or side effects of surgery such as infections and anesthetic incidents). Patients, whose fractures have not healed, will still be able to undergo surgical intervention at a later date. Assuming healing rates of 86% for surgical and 75% for LIPUS treatment, patients with incomplete fracture healing would be considered as treatment failures, included in the 14% or 25% unsuccessful treatment outcomes. Since no relevant side effects are to be expected from LIPUS treatment, the risk of delayed fracture-healing in the event of unsuccessful LIPUS treatment is therefore offset by the risk of unnecessary surgical intervention. The non-inferiority threshold of −25 percentage points is considered appropriate in this context.

With the above assumptions, a one-sided significance level of 2.5% and a power of 90%, 166 patients are required per group. In addition, a dropout rate of 10% is assumed. The proportion of dropouts of max. 10% appears realistic, as patients with non-unions require regular clinical and radiological check-ups (timed to coincide with the study visits) even without participating in the study. The intention-to-treat (ITT) analysis will be used to include patients who will not comply with the protocol. Based on the above assumptions, 184 patients will have to be recruited per treatment group. Accordingly, a total number of 370 cases will be required.

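### The DASH/LEFS score that anchors the improvement rule in the primary endpoint is taken after randomisation, from unblinded patients who know their arm

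*Protocol article*

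**What the plan says.** The order of events is in the protocol article under Participant timeline {13}. At screening the eligibility criteria are checked, and then "If these criteria are met, consent is obtained and the patient is randomized into one of the two groups". Arm-specific steps follow: the ultrasound device is prescribed, or the operation is prepared, with anaesthesia information given as an example. The text allows 7–21 days before the device arrives or a surgery date is set, and has a rule for gaps longer than four weeks. At the day-0 visit, "Before the start of LIPUS treatment or surgery, baseline data will be collected"; this is where pain (NRS), SF-12 and DASH or LEFS are completed.

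The day-0 score then enters the primary endpoint. For the arm, "the DASH must show an improvement of at least 10 points compared to baseline"; for the leg, "the LEFS must either show an improvement of at least 9 points compared to baseline". In both cases reaching the age- and sex-specific norm value is an alternative. Under Primary outcome, success requires functional restoration and bony consolidation together.

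The section Who will be blinded {17a} states that patients and treating investigators cannot be blinded. The safeguard it describes is an independent endpoint committee that views the last available X-ray or CT image.

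**The concern.** A baseline is protected by randomisation only if it is recorded before the allocation is known. Here the patient has learned, perhaps weeks earlier, whether an operation or a home device is coming. Disappointment, relief or anxiety before surgery could each change how limb function is rated, and not equally in the two arms.

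The score is not merely descriptive. It sets the starting point for a yes/no threshold. A baseline reported as worse makes the 10- or 9-point gain easier to reach, and one reported as better makes it harder. A difference between arms in baseline reporting therefore becomes a difference in the proportion healed, which is the quantity tested against the −25-point margin. The image committee protects the radiological half of the endpoint and has no bearing on a questionnaire. An analysis plan cannot repair this afterwards, because a score that was not collected before allocation cannot be recovered.

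**Working it through.** **1. Sequence.** Participant timeline {13} gives the order: consent, randomisation, device prescription or surgical preparation, possible wait, day-0 questionnaires, treatment. The text describes no DASH or LEFS before randomisation. The trial schedule (Fig. 2) is not visible in the version at hand; its caption mentions no earlier questionnaire.

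**2. The plan's own figure.** Inputs from Sample size {14}: an unpooled Z-test for non-inferiority; healing in 86% after surgery and 75% with LIPUS; a margin of 25 points. The stated result is: "With the above assumptions, a one-sided significance level of 2.5% and a power of 90%, 166 patients are required per group".

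n = [p_C(1−p_C) + p_T(1−p_T)] × (z_0.975 + z_0.90)² / (margin − (p_C − p_T))²

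= (0.1204 + 0.1875) × (1.960 + 1.282)² / 0.14² = 165.06, so 166 per group. This reproduces. Power at 166 is 90.2%. The timing of baseline does not enter this formula.

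**3. Illustration of size.** The document gives no distribution for the change in DASH, so these are assumptions: normally distributed change with SD 15–20 points; an arm-specific shift of 3 points in reported baseline; all patients on the DASH rule; every functional success achieved through improvement, not the norm value. Let f be the probability of functional restoration given consolidation, taken as 86–95% in both arms. Success needs both components, so the surgical composite of 86% requires f ≥ 86%.

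- Shifted functional rate: f′ = Φ(Φ⁻¹(f) + 3/SD).
- Consolidation rate: composite / f.
- Composite gain: (composite / f) × (f′ − f).
- P(declare non-inferiority) = Φ([0.25 − (p_C − p_T)] / SE − 1.960), with SE = √{[p_C(1−p_C) + p_T(1−p_T)] / 166}.

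*LIPUS baseline reported worse; true rates at the margin, 86% v 61%:*

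| f | SD | f′ | LIPUS composite gain (points) | One-sided error |
|---|---|---|---|---|
| 86% | 15 | 90.0% | 2.8 | 8.9% |
| 86% | 20 | 89.1% | 2.2 | 6.8% |
| 95% | 15 | 96.7% | 1.1 | 4.3% |
| 95% | 20 | 96.4% | 0.9 | 3.8% |

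Without a shift the error is 2.5%.

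*Surgical baseline reported worse; planned rates, 86% v 75%:*

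| f | SD | Surgical composite gain (points) | Power |
|---|---|---|---|
| 86% | 15 | 4.0 | 69% |
| 86% | 20 | 3.1 | 75% |
| 95% | 15 | 1.6 | 84% |
| 95% | 20 | 1.2 | 85% |

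In this direction the error at the margin falls below 2.5%, to about 0.2–1.3%.

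**The case against.** Day 0 has a rationale. The endpoint is timed from the start of treatment, and the score is taken before either treatment begins, so treatment itself has not altered it. The norm-value route bypasses baseline, and consolidation must also be present. The 12-month questionnaire is just as unblinded, and moving the baseline does not change that. All of this stands. It limits the size of the problem and the reach of the fix, but it does not explain why the reference score should follow allocation when a screening visit already exists.

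Several stronger readings are tempting and are not supported:

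- *The design favours LIPUS.* The document gives no direction. Anxiety before surgery would worsen the surgical baseline and work against LIPUS.
- *The error could reach about 14%.* That follows from assuming functional rates of about 60–75% and a 4-point gain in the LIPUS composite (86% v 65%). Functional rates that low cannot hold in a surgical arm with 86% composite success, and for LIPUS alone they would be a further assumption.
- *The score is an invalid covariate.* The models listed under Statistical methods {20a} include no baseline score.
- *Patients lost before day 0 break the ITT analysis.* They would normally lack the 12-month outcome too, and section {20c} has rules for missing primary-endpoint values.
- *The wait is usually one to three weeks or more.* The text says only that such time may elapse.

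**Conclusion.** The point holds as a possible bias of unknown direction and size. The sequence is clear in the text, subject to the schedule figure not being visible: the reference for the improvement rule is self-reported after allocation is known, and no described safeguard covers it. Under the assumptions above, a 3-point shift gives a one-sided error of about 4–9% in place of 2.5% if it favours LIPUS, or power of about 69–85% in place of 90% if it favours surgery. Success through the norm value would reduce these effects. The shift, the SD and the conditional functional rate are all assumed, so the ranges show only that a modest shift could matter. They do not show that one will occur. The change is an inexpensive improvement worth making; the point does not invalidate the design.

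**What to change.** Have patients complete DASH or LEFS, together with NRS and SF-12, at the screening visit after consent, and release randomisation in the eCRF only once these are entered. Name this score as the reference for the 10- and 9-point rules. Day-0 scores can be kept for description or for a sensitivity analysis of the primary endpoint.

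The cost is one set of short questionnaires moved to an existing visit and one eCRF check; randomisation already runs through the eCRF. The sample size does not change. The drawback is a baseline that may be a few weeks older, in fractures that are at least 6 months old at entry; the day-0 repeat would show whether that matters. The protocol should still acknowledge that the 12-month patient-reported score is open to open-label bias, which this change does not remove.

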**Fig. 2 Fig2:**
[figure not shown]
Trial schedule. *low-intensity pulsed ultrasound. **Numeric Rating Scale. ***Short Form-12. ****Disabilities of the Arm, Shoulder and Hand Questionnaire. *****Lower Extremity Functional Scale Questionnaire. ^a^If more than 4 weeks pass between screening and visit 0, the inclusion/exclusion criteria will be checked again and, at the discretion of the attending investigator, imaging will be repeated if necessary. ^b^X-ray/CT control for surgical planning (standard examination; may not be necessary if current imaging will be available that is sufficient for surgical planning. This will be at the discretion of the attending investigator). ^c^Postoperative complications that are attributable only to the surgery (e.g., wound infection) will be recorded accordingly only for the control group. ^d^Before starting the intervention, the correct location for LIPUS will be marked under X-ray control. ^e^If the bone is found to be consolidated (at least 3 out of 4 cortices will be radiologically confirmed to be consolidated) at visit 4, no further imaging will be performed unless this would be necessary at the investigator`s discretion. ^f^If full-weight bearing is possible, the time at which full weightbearing is reached will be documented

Visit 1 will take place as the first check-up 14 days after the start of the ultrasound treatment or after the operation. A physical examination will be carried out again and the range of motion, the weight-bearing capacity and the NRS will be documented. Patients will be asked about aids, supportive measures, medication taken, possible complications from the treatment and (serious) adverse events ((S)AEs) and (serious) adverse device effects ((S)ADEs) will be recorded.

Visits 2 to 4 will take place at around 6 weeks, 4 months and 6 months after baseline. Visit 5, which will take place 1 year after baseline, is the final visit. The dates correspond to the standard follow-up visits carried out during the treatment of non-unions. A physical examination will be carried out at all appointments, and the corresponding questionnaires will be given to the patient. All complications that will have occurred during treatment will be assessed. An X-ray or CT scan will be performed at the discretion of the investigator in accordance with routine treatment (Fig. 2).

